# Effectiveness and cost-effectiveness of a sustainable obesity prevention programme for preschool children delivered at scale ‘HENRY’ (Health, Exercise, Nutrition for the Really Young): protocol for the HENRY III cluster randomised controlled trial

**DOI:** 10.1136/bmjopen-2023-081861

**Published:** 2024-03-25

**Keywords:** Obesity, Community child health, Primary Prevention, PUBLIC HEALTH, Randomized Controlled Trial

## Abstract

**Introduction:**

One-fifth of children start school already overweight or living with obesity, with rates disproportionately impacting those living in the most deprived areas. Social, environmental and biological factors contribute to excess weight gain and programmes delivered in early years settings aim to support families to navigate these in order to prevent obesity. One of these programmes (Health, Exercise and Nutrition for the Really Young, HENRY) has been delivered in UK community venues (hereon named ‘centres’) in high deprivation areas since 2008 and aims to help families to provide a healthy start for their preschool children. We aim to establish the effectiveness and cost-effectiveness of HENRY, including its potential role from a wider systems perspective.

**Methods and analysis:**

This is a multicentre, open-labelled, two-group, prospective, cluster randomised controlled trial, with cost-effectiveness analysis, systems-based process evaluation and internal pilot. Primary analysis will compare body mass index (BMI) z-score at 12 months in children (n=984) whose parents have attended HENRY to those who have not attended. Secondary outcomes include parent and staff BMI and waist circumference, parenting efficacy, feeding, eating habits, quality of life, resource use and medium term (3 years) BMI z-scores (child and siblings). 82 centres in ~14 local authority areas will be randomised (1:1) to receive HENRY or continue with standard practice. Intention-to-treat analysis will compare outcomes using mixed effects linear regression. Economic evaluation will estimate a within-trial calculation of cost-per unit change in BMI z-score and longer-term trajectories to determine lifelong cost savings (long-term outcomes). A systems process evaluation will explore whether (and how) implementation of HENRY impacts (and is impacted by) the early years obesity system. An established parent advisory group will support delivery and dissemination.

**Ethics and dissemination:**

Ethical approval has been granted by the University of York, Health Sciences’ Research Governance Committee (HSRGC/2022/537/E). Dissemination includes policy reports, community resources, social media and academic outputs.

**Trial registration number:**

ISRCTN16529380.

STRENGTHS AND LIMITATIONS OF THIS STUDYThe Health, Exercise and Nutrition for the Really Young (HENRY) III trial provides an opportunity to examine the effectiveness and cost-effectiveness of an intervention that has been publicly funded and delivered at scale for more than 10 years, including short-term, medium-term and long-term outcomes.Our systems-based process evaluation will explore the role that community-based obesity prevention interventions play within the wider system, based on the understanding that factors that influence obesity are complex and multifaceted.The HENRY III trial has been designed following a successful feasibility study, in collaboration with local and national government partners, members of the public and a multidisciplinary trial team.The trial’s success is dependent on recruitment of local authority areas, where additional funding will be required to commission the intervention.A mitigation strategy has been developed to reduce the risk of selection bias inherent in cluster designs.

## Introduction

Reducing the prevalence of childhood obesity among people living in deprived areas is a public policy priority. Approximately one-third of children (27.7% on average and up to 34.5% in higher deprivation areas) are defined as overweight (13.3%) or having obesity (14.4%). Health inequalities have also broadened, from a 6.3% difference in rates of overweight and obesity between the most and least deprived areas in 2019/2020 to 10.7% in 2021/2022.^1 2^

Preventing excess weight in childhood is beneficial for health and well-being, as well as reducing medium-term to long-term burden on health services for those living with obesity, including mental health services and those used to treat and manage respiratory diseases such as asthma.^3 4^ Obesity prevention during childhood can also reduce excess weight gain and obesity in later life^5 6^ which is difficult to reverse once established^7–9^ and is a cause of numerous long-term, chronic health conditions. However, interventions to prevent obesity generally result in modest but inconsistent benefits.^7–10^ Given that obesity is caused by a wide range of physiological, psychological, environmental, economic and social factors, this is unsurprising and means that the role and cost-effectiveness of locally delivered programmes within a large and complex socioeconomic and public health system is uncertain. Public Health England advocated systems approaches; encouraging local areas to adopt a range of interconnecting interventions and policies inside and outside the healthcare sector to collectively tackle obesity and related health inequalities.^11^ It remains unknown what role individual interventions play in disrupting this system,^12^ and which of these interventions are most effective and cost-effective. Locally delivered public health prevention programmes can be cost-effective^13^; however, there is limited evidence specifically looking at obesity prevention delivered at scale. Further, while there has been an emergence of evidence that explores the role that understanding the obesity system has for adults^14–16^ since the Foresight map was published,^17^ there is a lack of understanding of what an early years obesity system looks like and what the implications of understanding this might be.

One childhood obesity prevention programme which has been delivered at scale for many years in the UK is HENRY (Health, Exercise and Nutrition for the Really Young); a community-based programme, designed to alter early years settings, upskill the early years workforce and improve lifestyle behaviours of parents/carers (hereon called ‘parents’) and their preschool aged (under 5 years old) children. Although HENRY was designed to be a universal programme, it has been predominantly delivered in children’s centres/community venues located in areas of high deprivation. Evidence suggests it has potential to impact on population obesity^18^ but its effectiveness is not yet established. The current trial adopts a novel approach to evaluate the effectiveness and cost-effectiveness of the programme and explore the potential role of HENRY in disrupting the multiple factors that influence excess weight gain in the system. This novel approach places an emphasis on exploring if and how HENRY influences the system in which it operates (including system balancers which may reduce its potential for population impact).

Following on from a successful feasibility study,^18^ our current evaluation will consider child obesity outcomes in the short-term (using data collected in the trial), medium-term (using routinely collected data at 3 years) and longer-term (using economic modelling and secondary datasets).

## Aims and objectives

### Aim

To establish the effectiveness and cost-effectiveness of an obesity prevention programme delivered at scale, including its potential role from a wider systems perspective.

### Primary objective of randomised controlled trial

The primary objective of the trial is to determine whether HENRY reduces child age-adjusted and sex-adjusted body mass index (BMI) at 12 months.

#### Secondary objectives of randomised controlled trial

To determine whether HENRY improves parent self-efficacy, eating behaviours, feeding behaviours, dental health and quality of life.To explore whether HENRY influences rates of obesity in parents, siblings and staff (health practitioners).To examine the social and physical environment in the children’s centres.To monitor any safety issues from the intervention, including adverse events or unintended consequences

### Internal pilot objectives of randomised controlled trial

To assess centre recruitment, parent recruitment and HENRY programme delivery against predefined progression criteria.

#### Economic evaluation objectives

To explore the long-term effects on child BMI.To determine whether HENRY provides an overall cost saving (eg, to the NHS).

#### Process evaluation objectives

To produce a map of the system within which HENRY operates and identify hypotheses about how this may be disrupted in response to HENRY.To analyse the system in which HENRY is embedded to understand how the system and its elements change over time in response to HENRY.To undertake a traditional process evaluation nested within the randomised controlled trial (RCT) to understand reach of HENRY within target population, potential contamination and how it has been implemented.

## Methods and analysis

### Trial design

A multicentre, open-labelled, two-group, prospective, cluster RCT, with cost-effectiveness analysis and embedded mixed methods complex systems evaluation and internal pilot (figure 1). 82 eligible children’s centres from within ~14 local authorities (depending on the number of centres per local authority) will be randomly allocated (1:1) to deliver HENRY or continue with standard practice (control). 984 eligible parents will be recruited.

**Figure 1 F1:**
[figure not shown]
Trial summary. FU, follow-up; HENRY, Health, Exercise and Nutrition for the Really Young; QoL, quality of life.

### Setting and recruitment

#### Local authority and centre recruitment

We plan to recruit local authorities or other associations (eg, NHS Trusts, private organisations) that are willing to commission HENRY across the UK, from which centres and parents will be recruited (figure 2). In addition to inviting areas who actively express an interest in the intervention (independently from the trial), we will promote the trial in partnership with all National Institute of Health Research (NIHR) Clinical Research Networks (CRN) in England and the equivalent organisations in the devolved nations. Eligible areas (criteria are detailed below) will then be asked to (1) nominate at least two (ideally six or more) centres which meet trial eligibility criteria and (2) sign an agreement before entering the trial. We will record reasons for declining participation, and basic demographic information, from those authorities that choose not to participate.

**Figure 2 F2:**
[figure not shown]
Flow of recruitment. CRN, Clinical Research Networks; CTRU, Clinical Trials Research Unit; HENRY, Health, Exercise and Nutrition for the Really Young.

Local authorities will be asked to nominate approximately twice the number of centres for which they wish to commission HENRY, so that approximately half can be randomised to receive HENRY and half can be randomised to control. Although there are no exclusions based on the demographics of centres, location will be monitored and commissioners encouraged to nominate centres to include a range of diverse social and environmental characteristics. Centre managers will be given information about the research and asked to provide consent for their centre to participate through a collaboration agreement.

### Parent/carer and staff recruitment

Centre staff will invite all parents who are booked to attend a HENRY programme to take part in the research (and will be remunerated per participant based on NIHR CRN service support costs^19^). If interested, they will be screened for eligibility and will be asked to provide informed consent to take part. Those who decline will still be able to attend the HENRY intervention if they wish. Screening and recruitment will aim to start at least 6 weeks prior to the start of each HENRY programme. Programmes typically enrol an average of eight parents, of whom our design aims to recruit an average of four parents. Once consented, blinded data collection staff will contact participants to arrange the baseline visit and complete trial registration. A similar process will recruit parents from the control centres. Here, parents who attend other programmes (eg, stay and play sessions) will be invited to take part within the same time frames. Parents will also have the opportunity to self-refer into the trial via recruitment posters displayed in the centres. A £30 shopping voucher will be offered to participants in recognition of their contribution (£15 at baseline, £15 at follow-up). Parent consent will include five options: consent to take part in the trial only, consent to provide height and weight measurements, consent to provide HENRY programme attendance data (if attending a HENRY programme), consent to be contacted about taking part in a process evaluation interview and consent to share routinely collected National Child Measurement Programme (NCMP) data after 3 years for the purposes of the economic evaluation.

Staff recruitment will occur once they have completed site training. Those agreeing to take part will provide their height, weight and waist circumference, which they can self-measure. Staff will also have the opportunity to consent to be contacted about taking part in a process evaluation interview.

### Eligibility criteria

Local authorities can be new to HENRY or already commissioning HENRY, provided they have at least two centres (ideally six) meeting centre eligibility criteria. Local authorities using external teams outside of the centre to deliver HENRY programmes (eg, health visitors) will be eligible, in addition to those wishing to train internal centre staff to deliver programmes (the most common model). Local authorities without coverage of a NIHR local CRN (LCRN; the teams responsible for collecting trial data from parents and staff) will not be eligible.

Centres: Any type of centre or other early years setting such as a nursery or community venue will be eligible to take part provided that they do not already deliver HENRY, and their staff have not received HENRY training (within the past 2 years). This includes both public and private nurseries. Centres where staff are shared between nominated centres will not be eligible. Centres must aim to run HENRY programmes starting within 12 weeks of training completion and plan to run three programmes during their trial participation period (approximately 18 months). They should be in geographically separate areas to protect against contamination (judged on a case by case basis) and managers must agree to support participant recruitment within their centres. If the centre operates as part of a cluster, that cluster must be deemed to be HENRY naive. HENRY naive clusters are defined as a group of centres within a cluster that does not include any centres that are (a) currently delivering HENRY or (b) have been trained to, or delivered HENRY within the past 2 years.

Centres that are either currently delivering HENRY or have previously delivered HENRY in the last 2 years are not eligible.

Parents/carers: The target population for the intervention is parents/carers of preschool children. Parents may not be registered more than once but they may be screened on more than one occasion if not registered following first screening, as both eligibility and willingness to participate may change. Parents must have at least 1 child aged 6 months to 5 years (18 months to 6 years at 12-month follow-up) at the time of starting the programme. If more than one child in a family fulfils eligibility criteria, the youngest child (by birth timing if twins) will be considered as the reference child (from which data will be collected). Parents must be willing to attend the programme sessions (intervention centres) and willing to provide data in accordance with the data collection protocol. Parents will be provided with full details of the data collection requirements in advance so that they can make informed decisions as to whether to participate. They must either speak English or bring their own interpreter with them (eg, family member) each time they need to respond to questionnaires for trial purposes. Where available, non-English-speaking parents will also be able to use local interpreters (provided by the centre or through the LCRN). Parents with severe learning difficulties that preclude them taking part in group sessions in which they need to be able to read and write will not be eligible. Those whose reference child is tube fed or with other known clinical conditions likely to affect growth over the period of the trial (eg, coeliac disease) and those who have attended a HENRY group for a previous child will also be ineligible.

We have developed a recruitment strategy based on learning from our feasibility study^18^ which includes screening and consenting by centre staff (who are familiar to families) and detailed training for centre staff, including clear timelines and expectations. For example, in order to meet targets, a minimum of four parents should be recruited within a 6-week window prior to the start of each HENRY programme (and at an equivalent time in control centres).

All centre staff will be invited to participate in the research including those directly and indirectly involved in delivering HENRY programmes.

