Quantitative process data will be gathered to summarise attendance and drop out by centre and overall and will support the monitoring and evaluation of contamination. Thus, in addition to exploring contamination through qualitative interviews, data on staff movement and sharing of HENRY related messages will be captured. Key to this will be an online HENRY-trained staff survey at two time periods (towards the end of the internal pilot and at the end of the RCT intervention period) asking whether, how and when staff shared HENRY practice outside their centre.

Qualitative data will be analysed prior to the trial outcome analysis using the framework approach. An initial thematic framework will be based on familiarisation of a range of transcripts, analysis of qualitative interviews from the feasibility study,^30^ and the process evaluation framework (mechanisms, context and implementation).^29^ Quantitative evaluation will combine trial and process data to apply a causality-based model of obesity prevention to develop a systems archetype.^31^ Analysis will incorporate Morphological Analysis and Fuzzy Cognitive Mapping techniques^32^ to evaluate and assign inter-relationships between components through causal weights and network directionality. We will examine the range of operating conditions of the HENRY system model to classify its overall dynamic behaviour (identifying which Systems Archetype HENRY most closely resembles^31^; providing a basis for comparison to other obesity models (eg, Foresight) to explain how HENRY may disrupt obesity prevalence in childhood).

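### The parent exclusion for earlier HENRY attendance covers only a previous child, so read literally it admits families who already attended for the reference child (minor)

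*Protocol article*

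**What the plan says.** All of the following is in the protocol article.

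- Eligibility criteria, parents/carers: "those who have attended a HENRY group for a previous child will also be ineligible". This is the only exclusion at family level that concerns earlier exposure to the programme.
- Same section: "Parents must have at least 1 child aged 6 months to 5 years", and where several children qualify, "the youngest child (by birth timing if twins) will be considered as the reference child".
- Same section: "Parents may not be registered more than once". This limits trial registration, not earlier programme attendance.
- Same section, local authorities: "Local authorities can be new to HENRY or already commissioning HENRY".
- Same section, centres: "Centres that are either currently delivering HENRY or have previously delivered HENRY in the last 2 years are not eligible". Clusters of centres must also be HENRY naive over the same 2 years, and centres should be geographically separate.
- Parent/carer and staff recruitment: in the intervention arm, "Centre staff will invite all parents who are booked to attend a HENRY programme to take part in the research". Control parents are invited from other activities, such as stay and play.
- Systems-based process evaluation: the quantitative contamination data cover staff movement, message sharing and a survey of HENRY-trained staff "asking whether, how and when staff shared HENRY practice outside their centre".

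**The concern.** The evident purpose of the exclusion is to keep out families who have already had the programme. As worded, it stops exposure that reached the family through an older sibling but not exposure with the measured child. A parent with one child, who attended when that child was a baby, passes the criterion.

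If such parents enter the control arm, some control children carry part of the programme's effect. The primary analysis is by intention to treat, so the contrast between HENRY and standard practice would shrink towards zero. A null result would then be slightly harder to interpret.

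**Working it through.** **Can such families exist?**

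1. Authorities already commissioning HENRY are eligible, so other venues in the same authority may be delivering it. The active intervention sections describe delivery in schools and places of worship, and remotely.
2. The centre look-back is 2 years and the child may be up to 5. For the oldest children, up to 5 − 2 = 3 years of life fall outside the look-back, even at a trial centre.
3. The HENRY-naive rules describe centres and clusters of centres. They do not screen the individual family.

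**Which arm would they be in?** Intervention parents are approached because they have booked HENRY; control parents are approached at general sessions. A parent who has completed the course for this child has little reason to book it again but may still use general sessions. This is an inference from the recruitment routes. The documents report nothing on repeat booking, and nothing bars a repeat attender from the HENRY arm.

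**Reproducing the stated power.** Inputs from Sample size: 41 centres per arm, 12 parents per centre, 20% loss, ICC 0.03, coefficient of variation 0.48, effect 0.27 SD. The two-sided 5% level is in Data analysis plan.

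- Retained cluster size: 12 × 0.8 = 9.6
- Design effect: 1 + [(1 + 0.48²) × 9.6 − 1] × 0.03 = 1.324
- Effective n per arm: 41 × 9.6 / 1.324 = 297.2
- Power: Φ(0.27 / √(2/297.2) − 1.96) = 0.908 (0.902 using t with 80 df)

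The stated 90% is reproduced, so the sample size contains no arithmetic error.

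**Effect of exposed controls.** Let p be the share of control parents already exposed with the reference child, and c the fraction of the effect carried over. Assume no exposed parents in the HENRY arm. The detectable contrast is 0.27 × (1 − pc). Both p and c are assumptions; the documents give neither. There are 492 control parents (984 / 2).

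| p | Control parents | Effect, c = 1 | Power, c = 1 | Power, c = 0.5 |
|---|---|---|---|---|
| 0 | 0 | 0.270 | 0.908 | 0.908 |
| 2% | 10 | 0.265 | 0.897 | 0.903 |
| 5% | 25 | 0.257 | 0.878 | 0.894 |
| 10% | 49 | 0.243 | 0.842 | 0.878 |

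**How large might p be?** Active intervention reports about 24,500 parents reached since 2008 in more than 50 areas. That is at most 24,500 / 50 = 490 per area on average, or about 33 a year over roughly 15 years. Over about 4.5 years of a child's possible exposure this is about 150 families per area. If an authority has 5,000 to 15,000 under-fives (an assumption, not in the documents), the share is about 3% to 1%. It is a rough guide: uptake is uneven, and users of children's centres may be exposed more often than families in general. Authorities new to HENRY would pull the trial-wide figure down.

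**The case against.** The strongest case against is that this is a wording slip with little consequence. Much of it stands.

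- The 2-year rule, naive clusters and geographic separation narrow the routes. Earlier attenders who went with an older child are already excluded.
- Full carry-over is a worst case. The primary model adjusts for baseline BMI z-score, which absorbs part of an effect already present at entry.
- The reach figures point to a low share, so an exposed share of 10% is towards the pessimistic end.

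A reader might go further than the documents allow in three ways.

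- That exposed families would gather mainly in the control arm. The recruitment routes make this plausible, but no figure shows it. Parents who decline the research may still attend HENRY at intervention centres and can be screened again there.
- That power could fall to about 75%. This needs 20% of control parents exposed with full carry-over, and nothing in the documents supports such a share.
- That the trial could not detect the problem. Contamination is a stated process-evaluation topic, and a sensitivity analysis would drop affected control centres. The supplementary outcome table and the screening form are not at hand, so one can say only that no data item described in the article asks control parents about their own attendance.

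What remains is the rule itself. It is stated explicitly and drawn too narrowly, so it is not detail left to a fuller document. The centre-level sensitivity analysis is not built for single families exposed elsewhere.

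**Conclusion.** The point holds as a minor flaw in a stated eligibility rule. Confidence is high that the literal wording admits parents who attended HENRY for the reference child, and moderate that they would be more frequent among controls. Any bias would be modest and towards no effect.

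Its size depends on an exposed share and a carry-over that the documents do not give. At a share of 2% to 5%, power falls by about 1 to 3 percentage points even with full carry-over. The sample size calculation is not in question.

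**What to change.** Reword the exclusion so that it covers parents who have attended a HENRY group, in person or online, for any child including the reference child. Ask the question at screening in the same way in both arms.

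The cost is one eligibility phrase and one screening question. A few parents in already-commissioning authorities become ineligible.

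HENRY attendance by control parents after registration is a separate contamination issue that eligibility wording cannot solve. An optional addition is one question to all parents at 12 months about attendance since registration. It should be self-completed after the measurements, since most questionnaires at home visits are interviewer administered and the assessor should stay blinded.
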